###### STATISTICAL EVALUATION

1. Power Analysis

A power analysis was conducted. With a goal for =0.20, and two-tailed =0.05, the pilot studies previously conducted for the mania registration trials suggested that a mean change in MADRS scores were 20 points improved with ziprasidone compared to placebo. Given the few patients in the placebo arm, we conducted this power analysis with a smaller expected effect size, using a high projected mean difference of 10 points, and a low projected mean difference of 5 points. Based on the available pilot data, a projected standard error of the mean difference was assumed to be range from equivalent to the mean difference to twice as much as the mean difference (5-15 points). Using an internet-based power analysis software program, we conducted the power analysis noted in the table.

To assess various levels of effect size, power, and standard deviation, a sensitivity analysis was conducted (Table). As indicated by the table, if the mean difference is small and the standard deviation is large, then very large samples would be needed. However, if the same or larger effect was seen with somewhat larger standard deviation, the total sample size required would range from 26 to 138 patients. Thus, unless the true mean difference is quite minimal, a sample size in that range should have a good chance of detecting a real effect.

Table. Sensitivity analysis for sample size calculation

| Sample size (per arm) | Effect size (Mean difference in MADRS) | Standard deviation within each group | Power |
| --- | --- | --- | --- |
| 13 | 5 | 5 | .80 |
| 50 | 5 | 10 | .80 |
| 69 | 5 | 10 | .90 |
| 112 | 5 | 15 | .80 |
| 30 | 10 | 5 | .90 |
| 13 | 10 | 10 | .80 |
| 18 | 10 | 10 | .90 |
| 29 | 10 | 15 | .80 |
| 5 | 20 | 10 | .90 |

Therefore, a sample size of about 100 patients should be optimal for this study. This would be best accomplished in 4 sites, with a goal of accrual of 25 patients per site. At an average recruitment of about 2 patients per month, this could be achieved in one year of recruitment.

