It should be noted that this study of the depressive mixed state differs from a study of “agitated depression”. The concept of agitated depression does not have a consensus definition; usually it entails a major depressive episode with at least psychomotor agitation. The depressive mixed state, on the other hand, is defined as more than simply psychomotor agitation along with depression: there must also be one or two other manic symptoms (depending on the definition). Three more manic symptoms would define the condition as a DSM-IV mixed episode. Thus the depressive mixed state is a subthreshold DSM-IV mixed episode.

Studies suggest that the majority of persons with a depressive mixed state have bipolar disorder type II, but a substantial group will also have unipolar depression, according to DSM-IV criteria [7].

Ziprasidone appeared to be especially effective in treating manic patients who met DSM-IV criteria for a mixed episode in its registration trials. Due to unequal sample sizes in randomized groups, however, only 4 patients were randomized to placebo among those with mixed episodes (Pfizer, data on file). Nonetheless, those pilot data, along with the biochemical effects of ziprasidone on serotonergic neurotransmission, support the potentially selective utility of this agent in those with a mixture of manic and depressive symptoms.

The purpose of the proposed study is to examine the efficacy of ziprasidone for the depressive mixed state in patients with bipolar or unipolar depression. This will be the first double-blind RCT in the depressive mixed state. Pfizer is sponsoring this study.

.

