## STUDY OBJECTIVES

The primary outcome of this study is to determine if ziprasidone is effective for the depressive mixed state in bipolar and unipolar depression.

1. **STUDY DESIGN**

This will be a four-site, block randomized (1:1 ratio) double-blind, placebo-controlled prospective study in which 100 patients will be enrolled. Patients will be randomized to ziprasidone or placebo in the 6 week acute phase of the study. Randomization will be stratified by three factors: subtype of depressive disorder (bipolar type II vs. unipolar), presence or absence of rapid cycling and duration of current MDE (< vs. > 3 months). The primary outcome measure will be change from baseline Montgomery-Asberg Depression Rating Scale scores in the acute phase. Enrollment will occur over 12 months.

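### The power section calls its variability input a standard error of the difference but uses it as a within-group SD, and the .80 power at 50 per arm for 5 points is not supported on either reading.

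*Protocol*

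**What the plan says.** All of this stands in the protocol, Statistical Evaluation, Power Analysis, unless another section is named.

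- **Error rates.** The goal is a type II error of "0.20, and two-tailed" alpha of 0.05 (the Greek letters are lost in the text), so 80% power with a two-sided test.
- **Effect.** The calculation was done "using a high projected mean difference of 10 points, and a low projected mean difference of 5 points". The pilot difference was 20 points. It was set aside because the placebo arm was so small: "only 4 patients were randomized to placebo among those with mixed episodes" (Background and Rationale).
- **Variability, in the text.** Citing pilot data, the section says "a projected standard error of the mean difference was assumed to be range from equivalent to the mean difference to twice as much as the" (same difference), with 5-15 points in brackets.
- **Variability, in the next paragraph and the table.** "To assess various levels of effect size, power, and standard deviation, a sensitivity analysis was conducted", and the table column that holds 5, 10 and 15 is headed "Standard deviation within each group".
- **Conclusion.** The text quotes a total of 26 to 138 patients and ends: "Therefore, a sample size of about 100 patients should be optimal for this study". With 1:1 allocation (Study Design), that is the row with 50 per arm, difference 5, SD 10, power .80.

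**The concern.** The same three numbers carry two names. The standard error of a difference between two means is the within-group SD multiplied by sqrt(1/n1 + 1/n2), so one cannot stand in for the other without the arm sizes. No conversion, pilot SD or ziprasidone arm size is given. A reader therefore cannot tell where the SD of 10 in the decisive row comes from.

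What is at stake is the claim that about 100 patients gives good power unless the true difference is very small. If the input or the calculation behind the .80 is wrong, that claim fails, and a null result would be read as stronger evidence of no effect than it is.

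**Working it through.** **1. The printed row.** Inputs from the table: n = 50 per arm, difference 5, SD 10, so the standardised effect is 0.5. Normal approximation: n per arm = 2 × (z_alpha + z_power)² / 0.5².

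- One-sided 0.05: 2 × (1.645 + 0.842)² / 0.25 = 49.5, so 50 per arm. This is the printed figure.
- Two-sided 0.05, as the text states: 2 × (1.960 + 0.842)² / 0.25 = 62.8, so 63 per arm (126 in total).

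Power of the unpaired t-test at 50 per arm (noncentral t) is 79.9% one-sided and 69.7% two-sided. The printed .80 is therefore a one-sided result. Eight of the nine rows reproduce one-sided, within a patient. Two-sided, only the 20-point row comes close (6 against 5). The row with 30 per arm, 10 points, SD 5, power .90 reproduces neither way (5 one-sided, 6 two-sided).

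**2. The range against its rule.** One to two times 5 is 5-10, and one to two times 10 is 10-20. Together they give 5-20, not 5-15. The table has no 10-point row with 20, and it has two rows outside the rule: 10 points with 5 (half) and 5 points with 15 (three times).

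**3. If 10 is the within-group SD.** Two-sided power for 5 points at 50 per arm is 69.7%. The difference detectable with 80% power is SD × sqrt(2/50) × (1.984 + 0.845) = 10 × 0.2 × 2.829 = 5.7 points.

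**4. If the input is literally a pilot standard error.** SD = SE / sqrt(1/4 + 1/m), with 4 placebo patients. The ziprasidone number m is not given, so I assume anything from 4 to very large; the divisor then runs from 0.71 down to 0.50. Two-sided t-test power at 50 per arm:

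| Input read as SE | Implied SD | Power, 5 points | Power, 10 points |
| --- | --- | --- | --- |
| 5 | 7.1-10.0 | 94%-70% | over 99% |
| 10 | 14.1-20.0 | 42%-24% | 94%-70% |
| 15 | 21.2-30.0 | 22%-13% (normal approximation) | 65%-38% |

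The detectable difference at 80% power, by the formula in step 3, is 4.0-5.7 points for SE 5 and 8.0-11.3 points for SE 10.

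**5. If it were the standard error of the planned trial.** An SE equal to the difference gives a z of 1 and 17% two-sided power; an SE of twice the difference gives 8%. Nobody would plan a trial on that, so this reading can be set aside.

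**The case against.** The best reply is that this is a slip of the pen and that SD was meant throughout. Much supports it. The value is projected and assumed, and it is scaled to the 5- and 10-point differences rather than to the pilot's 20 points, for which one to two times would be 20-40. The following paragraph and the table header both say standard deviation. The total of 26 to 138 patients is exactly twice 13 and twice 69, and those rows have an SD of one or two times the difference. I accept that SD is the likelier meaning.

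A reader might infer something stronger: that a real pilot standard error was entered as an SD, so that the planning SD is too small. The document does not support that. It reports no pilot standard error, pilot SD or ziprasidone arm size. Even on the literal reading, an SE of 5 implies an SD of 7.1-10, no larger than the 10 behind the sample size.

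Two further points also stand. The missing row of 10 points with SD 20 has the same standardised effect as 5 points with SD 10, so adding it would not change the sample size. The table does show the harsher case of 5 points with SD 15 (112 per arm), and the text warns that a small difference with a large SD needs very large samples.

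The slip explanation does not rescue the .80. With 10 taken as the SD, two-tailed power is still about 70%.

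**Conclusion.** The point holds as an inconsistency in the stated basis for 100 patients. The text names one quantity and the table uses another, and the stated range does not follow from the stated rule. These two faults need no assumption.

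The printed .80 for 5 points at 50 per arm is not supported under the two-tailed 0.05 test. Power is about 70% if 10 is the within-group SD, which needs only the plan's own inputs. It is about 24-42% if 10 is a pilot standard error, which assumes 4 placebo patients and a ziprasidone arm between 4 and very large. The lower range is conditional and should not be quoted as the trial's power. For a 10-point difference with SD 10 or 15, power at 50 per arm remains above 90% two-sided.

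**What to change.** In the Power Analysis:

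1. State that the input is the within-group SD of MADRS change and give its source. If it really is a standard error, convert it with SD = SE / sqrt(1/n1 + 1/n2), using the pilot arm sizes.
2. Make the range agree with the rule (5-20), or change the rule, and choose the table rows to match.
3. Recompute the table with the two-tailed 0.05 test, including the row with 30 per arm, which is wrong under either sidedness.
4. Keep 100 patients, but drop the claim that this number is optimal. State instead the power at 50 per arm (about 70% for 5 points at SD 10) and the difference detectable with 80% power (about 5.7 points at SD 10). The figure of 8.0-11.3 points applies only if the 10 proves to be a standard error.

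The cost is a recalculation and a few sentences, with no extra patients. The downside is a less favourable stated power.

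### The claim that only minimal differences would be missed drops the SD condition: at SD 15, 100 patients have about 38% power for the protocol's own 5-point projection

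*Protocol*

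**What the plan says.** The Power Analysis under Statistical Evaluation sets a significance level of "two-tailed =0.05" and a target of "With a goal for =0.20". The Greek letters are lost in the text; the second figure is read as a type II error of 0.20, that is, power 0.80. The effect assumption is set by "using a high projected mean difference of 10 points, and a low projected mean difference of 5 points", and the spread is taken as 5 to 15 points. A nine-row table then gives patients per arm by difference, within-group SD and power.

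Three statements follow:

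- A caveat: "if the mean difference is small and the standard deviation is large, then very large samples would be needed".
- A contrast, for an equal or larger effect: "with somewhat larger standard deviation, the total sample size required would range from 26 to 138 patients".
- A conclusion: "unless the true mean difference is quite minimal, a sample size in that range should have a good chance of detecting a real effect".

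About 100 patients is then called the best size. The Study Design section allocates them 1:1, so 50 per arm.

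**The concern.** The conclusion makes detection depend on the size of the true difference alone. In the table it depends on the ratio of difference to SD, and the caveat two sentences earlier says so. Five points is the protocol's low planning value and SD 15 is the top of its planning range. Nothing calls 5 points minimal, yet the table asks for 112 per arm in that case.

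The contrast sentence does not help. It follows a case with a large SD and speaks of a somewhat larger one, but the rows behind its range have SD 10. That is larger than the table's SD of 5 and smaller than its 15. A reader has to work back from the table to learn which SD the range assumes.

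At stake is the stated reason for 100 patients, and what a non-significant result could later be said to exclude.

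**Working it through.** **Inputs** (Power Analysis and its table): differences of 5 and 10 points; within-group SDs of 10 and 15; two-tailed 0.05; 50 per arm. The planned unpaired t-test is in Outcome Measures and Planned Analyses.

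**1. Where 26 to 138 comes from.** The SD 10 rows for 5 and 10 points are 13, 18, 50 and 69 per arm. Doubled, they give 26, 36, 100 and 138. The range is exactly their span.

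**2. Which significance level the table used.** By normal approximation, n per arm = 2(z_α + z_β)²(SD/difference)².

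- 5 points, SD 10, power 0.80, one-sided: 2(1.645 + 0.842)² × 4 = 49.5, so 50, as printed.
- The same, two-sided: 2(1.960 + 0.842)² × 4 = 62.8, so 63.

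Eight of the nine rows reproduce within one patient per arm at one-sided 0.05. Seven of those eight fail at two-sided 0.05. The eighth (20 points, SD 10) is too small to discriminate: 5 against 6. The ninth (10 points, SD 5, power 0.90, printed as 30) reproduces either way at no value near 30; the formula gives 5 or 6.

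**3. Requirements at the stated two-tailed 0.05** (t-test, noncentral t, rounded up per arm):

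| Difference | SD | Power | Printed total | Two-tailed total |
| --- | --- | --- | --- | --- |
| 10 | 10 | 0.80 | 26 | 2 × 17 = 34 |
| 10 | 10 | 0.90 | 36 | 2 × 23 = 46 |
| 5 | 10 | 0.80 | 100 | 2 × 64 = 128 |
| 5 | 10 | 0.90 | 138 | 2 × 86 = 172 |
| 10 | 15 | 0.80 | 58 | 2 × 37 = 74 |
| 5 | 15 | 0.80 | 224 | 2 × 143 = 286 |

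The SD 10 range is therefore 34 to 172. The normal approximation gives 32 to 170, and 72 and 284 at SD 15.

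**4. Power of 100 patients.** With n = 50 per arm there are 98 degrees of freedom and the noncentrality is (difference/SD) × √(50/2) = 5 × difference/SD.

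| Difference | SD | Noncentrality | Two-sided power | One-sided power |
| --- | --- | --- | --- | --- |
| 5 | 10 | 2.50 | 0.70 | 0.80 |
| 5 | 15 | 1.67 | 0.38 | 0.50 |
| 10 | 15 | 3.33 | 0.91 | 0.95 |

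At the top of the quoted range, 138 patients (69 per arm), power for 5 points at SD 15 is 0.49 two-sided and 0.62 one-sided.

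**5. Difference detectable with 80% power at 50 per arm, two-sided.** About 5.7 points at SD 10 and 8.5 points at SD 15. The one-sided values are 5.0 and 7.5.

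**The case against.** The strongest defence is that the text discloses the difficult case. It says that a small difference with a large SD needs very large samples, and it prints the row of 112 per arm. In a table that runs SD 5, 10, 15, an SD of 10 can fairly be called somewhat larger than 5, and the doubling is correct. The 100 patients match a printed row (5 points, SD 10, power 0.80) and do not depend on SD 15.

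Most of this stands, and it limits the point. A reader might infer that the SD 15 rows contradict the range of 26 to 138, or that the range sentence runs in the wrong direction. The documents do not support that. The total of 58 for 10 points lies inside the range, and 224 for 5 points is the case already conceded. The range sentence is ambiguous about its SD, but its figures agree with the table. Nor is low power at 26 patients an argument against the trial, which enrols 100.

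The defence does not cover the conclusion, which drops the SD condition and excepts only very small differences. The match with a printed row also holds only one-sided, while the text says two-tailed.

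**Conclusion.** The point holds as an overstated property of the design. At the stated level, 100 patients are adequate for 10 points at SD 15 (0.91), short of the 0.80 target for 5 points at SD 10 (0.70), and weak for 5 points at SD 15 (0.38). If the SD is 15, true differences up to about 8.5 points have less than 80% power, and most of the 5-to-10-point planning range lies below that.

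The failure at 5 points and SD 15 does not depend on sidedness: one-sided power is still only 0.50. It would go too far to say that such an effect is missed more often than not under either convention, since one-sided power is just above one half. It would also go too far to say that 100 patients is an indefensible number. What fails is the stated reason for it.

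Assumptions: the 5 to 15 points are within-group SDs, as in the table heading (the text calls them a standard error of the mean difference); all 100 patients contribute, as the section makes no allowance for dropout; and the unadjusted t-test is used. The mixed-effects model also planned could be more precise, but the protocol gives no figure for that.

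**What to change.** In the Power Analysis:

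1. Say that the quoted range applies to SD 10 with differences of 5 to 10 points.
2. Recompute the table and range at the stated two-tailed 0.05. By t-test the totals are about 34 to 172 at SD 10, and about 74 (10 points) and 286 (5 points) at SD 15. The printed totals should not be carried over, because they are one-sided. Correct the row for 10 points, SD 5, power 0.90 at the same time.
3. State the power of 100 patients: about 0.70 for 5 points at SD 10, 0.38 for 5 points at SD 15, and 0.91 for 10 points at SD 15.
4. Replace the clause that excepts only very small differences with a statement that a 5-point difference is not reliably detectable if the SD is near 15.

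The cost is a revised table and a few sentences. Enrolment need not change, but the stated justification for 100 becomes less favourable.

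### The sample-size table fits a one-sided test although the text says two-tailed 0.05: 50 per arm gives about 70% power, not 80%, and one row cannot be reproduced

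*Protocol*

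**What the plan says.** All of this stands in the Protocol, Statistical Evaluation, Power Analysis, to which the Number of Subjects section refers the reader.

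- **Error rates:** the targets read "0.20, and two-tailed" 0.05. The Greek letters are lost in the text, but beta and alpha are clear from context.
- **Effect:** the analysis was run "using a high projected mean difference of 10 points, and a low projected mean difference of 5 points".
- **Spread:** the text says that "a projected standard error of the mean difference was assumed to be range from equivalent to the mean difference to twice as much"; both multiples refer to that difference, and a range of 5 to 15 points is added. The table column is headed "Standard deviation within each group" and uses 5, 10 and 15.
- **Conclusion from the table:** "the total sample size required would range from 26 to 138 patients". These are twice the 13 and 69 per-arm rows.
- **Choice of size:** "Therefore, a sample size of about 100 patients should be optimal for this study".

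The allocation is 1:1 (Study Design). The primary comparison is an unpaired t-test, together with a mixed effects regression (Outcome Measures and Planned Analyses). The Protocol mentions no one-sided test anywhere.

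**The concern.** A familiar benchmark gives it away: half a standard deviation at 80% power and two-sided 5% needs about 64 per arm, and the table shows 50. If the whole table was run one-sided, every power figure a reader takes from it is too high for the design described in the text. The planned 100 patients coincide with exactly one row, the 5-point, SD 10, 80% row. An ethics committee, or a later reader of a null result, would then credit the trial with 80% power at the lower projected effect when it does not have it.

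Two further faults make the table hard to trust. One row asks for more patients at a smaller SD than a neighbouring row does at a larger one. And the text and table name different quantities for the spread.

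**Working it through.** **Inputs.** Alpha 0.05 two-tailed, power .80 or .90, 1:1 allocation, unpaired t-test, and the differences and SDs as listed in the table. No dropout allowance, since the Protocol states none.

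**Formula.** Normal approximation per arm: n = 2(z_a + z_b)² / d², with d = difference / SD. Here z_a = 1.645 one-sided or 1.960 two-sided, and z_b = 0.842 (.80) or 1.282 (.90). The t-test figures come from the noncentral t distribution.

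**The plan's own figure first.** For 5 points, SD 10, .80, d = 0.5:
- one-sided: 2(1.645 + 0.842)² / 0.25 = 49.5, so 50 per arm, as in the table;
- two-sided: 2(1.960 + 0.842)² / 0.25 = 62.8, so 63 per arm (64 with the t-test), a total of 128.

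**All nine rows.** The one-sided column is the unrounded t-test solution. The two-sided n is the smallest whole number that reaches the stated power.

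| Difference / SD / power | n in table | One-sided t | Two-sided t | Two-sided power at table n |
| --- | --- | --- | --- | --- |
| 5 / 5 / .80 | 13 | 13.1 | 17 | .69 |
| 5 / 10 / .80 | 50 | 50.2 | 64 | .70 |
| 5 / 10 / .90 | 69 | 69.2 | 86 | .83 |
| 5 / 15 / .80 | 112 | 112.0 | 143 | .70 |
| 10 / 5 / .90 | 30 | 5.1 | 7 | >.999 |
| 10 / 10 / .80 | 13 | 13.1 | 17 | .69 |
| 10 / 10 / .90 | 18 | 17.9 | 23 | .83 |
| 10 / 15 / .80 | 29 | 28.5 | 37 | .70 |
| 20 / 10 / .90 | 5 | 5.1 | 7 | .79 |

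Rounded to the nearest whole patient, the one-sided solution gives the table's n in eight of the nine rows.

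**The range.** 2 × 13 = 26 and 2 × 69 = 138 reproduce the quoted limits. Two-sided they become 2 × 17 = 34 and 2 × 86 = 172.

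**The odd row.** With d = 10/5 = 2 and power .90, the formula gives 4.3 one-sided or 5.3 two-sided. The t-test needs 5 to 7. For 30 per arm to be right at 10 points and 90% power, the SD would have to be about 13.1 (one-sided) or 11.7 (two-sided), not 5. The table also contradicts itself here: with the same difference and power, the larger SD of 10 needs only 18.

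**What 50 per arm delivers, two-sided t-test.**
- 5 points, SD 10: 69.7% (one-sided 79.9%). 80% is reached at 5.7 points.
- 5 points, SD 15: 38%.
- 10 points, SD 15: 91%.
- 10 points, SD 10: over 99%.
- 10 points, SD 20: 70%, because d is again 0.5.

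**Spread.** One to two times a difference of 5 or 10 covers 5 to 20 points, whereas the parenthesis says 5 to 15. The table's SDs keep to 5 to 15, but as multiples of the difference they run from 0.5 (5/10 and 10/20) to 3 (15/5). The 10-point, SD 20 case, which the verbal rule includes, is absent. A true standard error of one to two times the difference would mean power of only about 17% to 8%, so a standard error cannot have been meant.

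**The case against.** The central arithmetic is hard to dispute, so the best case on the other side concerns weight.

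- **No row is named as the design assumption.** The text gives a range, speaks of a good chance of detection, and supports 100 with four sites and one year of accrual. This is true, and 100 also lies inside the corrected range of 34 to 172. But the accrual argument shows that 100 is feasible, not that it is sufficient, and the only row equal to 100 in total is the 50-per-arm row.
- **The 30% miss rate belongs to one scenario.** This stands: it applies to 5 points at SD 10. At 10 points the trial is well powered. Still, 5 points is the Protocol's own low projection.
- **Standard error is a slip of the pen.** Very likely: the next paragraph and the table header both say standard deviation, and the 5-to-15-point range matches the table. What remains is a wrong label, and multiples that disagree with the point range in the same sentence.
- **The last row barely discriminates.** This stands: 5 against 6 by the normal approximation is close either way. The case rests on the other seven rows, where the shortfall reaches 31 per arm.
- **The odd row may hold a mistyped SD, difference or power rather than a wrong n.** The document cannot settle this. For the inputs as printed, 7 is the right n.

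**Conclusion.** The point holds. The stated two-tailed 0.05 and the table are incompatible. That the table was run one-sided is an inference, but eight matching rows make it a firm one. For the scenario that matches the planned 100 patients, power is about 70% and the false-negative risk about 30%, half as large again as the stated 20%. One row is wrong under either convention, and the spread is mislabelled.

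The figures assume an unpaired t-test, equal SDs and 50 evaluable patients per arm. If 20% to 30% had no endpoint value and were left out of the comparison (an assumption; the Protocol gives no rate), 40 to 35 per arm would remain, and power for 5 points at SD 10 would be about 60% to 54%. The main finding does not depend on that.

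**What to change.** Keep 100 patients and correct the Power Analysis:

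1. State the power of the chosen size, for example: *With 50 per arm and a two-sided 5% t-test, power is 70% for 5 points at SD 10 (80% for 5.7 points), 91% for 10 points at SD 15 and 38% for 5 points at SD 15.*
2. Replace the per-arm column, in row order, with 17, 64, 86, 143, 7, 17, 23, 37, 7. For the fifth row, first check whether the printed difference, SD and power are the intended ones. If they are not, correct or delete the row.
3. Change the total range from 26–138 to 34–172.
4. Call the spread the within-group standard deviation of the change, and describe it by the values actually used (5, 10 and 15 points), dropping the multiples that do not fit.

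The cost is protocol wording and a less favourable stated power. No patients, visits or analyses are added.

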###### STUDY POPULATION

#### Number of Subjects

We plan on enrolling 100 subjects overall, 25 subjects at the Tufts Medical Center site. A full power analysis is provided in section VIIIA.

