### Randomization Method

Randomization will occur with randomly generated computer lists held at the Duke site. All patients will be stratified by the following characteristics in block randomization:

Subtype of depressive disorder (bipolar type II vs. unipolar), presence or absence of rapid cycling, and duration of current MDE (< vs. > 3 months). These features may be unequally distributed in a small (<50) randomized study and could lead to high placebo response if type II, rapid cycling, or short duration episodes are overrepresented in the placebo group. Stratification will ensure control of these factors.

1. Outcome Measures and Planned Analyses

The a priori primary outcome measure will be change from baseline in MADRS scores in the acute phase. A priori secondary measures will be change from baseline in HAM-A, MRS, and other scores. The primary analysis for the acute phase between group effect size (for ziprasidone vs. placebo) will be obtained by unpaired t-test comparison and by mixed effects regression modeling. A priori subgroup analysis in rapid cyclers versus nonrapid cyclers, unipolar vs. bipolar subtypes, and shorter versus longer duration episodes, is also planned.

1. Definition of Evaluable Subject (Safety and Efficacy)

Subjects will be defined as able to be evaluated by two methods. The primary method will be an intent-to-treat analysis, including those who discontinue drug due to lack of efficacy or due to side effects. The secondary method will be completer analysis.

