### Quality Assurance Audits

Charts will be made available as requested to the sponsor, the participating site IRBs, and the FDA or other federal regulatory bodies for quality assurance purposes.

1. Study Discontinuation/Termination

Patients will be discontinued from the study for the following reasons:

1. 30% worsening of MADRS compared to baseline on two successive visits
2. MRS > 20 in two successive visits
3. Worsening of suicidal ideation (SI) as determined by MADRS suicide item  3 in two successive visits.
4. Clinical worsening sufficient to require hospitalization or other medication interventions in the judgment of the treating psychiatrist
5. Patient noncompliance with medications or appointments
6. Patient preference

After study termination, subjects who do well will receive Geodon. Subjects who do not do well will have the option of receiving Geodon. The blind will be broken only if there is a medical emergency.

D. Serious Adverse Event Reporting

For those studies where the principal investigator is required to report serious adverse advents (SAEs) to Pfizer, the investigator must use the enclosed Serious Adverse Event Fax Cover Sheet together with the FDA’s MEDWATCH form FDA 3500A (for mandatory reporting) which can be downloaded at [www.FDA.gov](http://www.FDA.gov/).

Reporting of Serious Adverse Events: Within 24 hours of first awareness of the event (immediately if the event is fatal or life-threatening), Principal Investigator will report to Pfizer by facsimile any Serious Adverse Event (“SAE,” as defined below) that occurs during the SAE reporting period (as defined below) in a Study subject assigned to receive the Pfizer Product (see Section 5, Pfizer Product). Principal Investigator will report such SAEs using an FDA MEDWATCH form and the *Serious Adverse Event Fax Cover Sheet* provided by Pfizer. SAEs should be reported as soon as they are determined to meet the definition, even if complete information is not yet available. SAEs will be reported to the Tufts Medical Center IRB on the same schedule as the study sponsor.

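### The 100 patients to be enrolled match the table's 50-per-arm row with no allowance for dropout, so a power that is only about 70% at the stated two-tailed 0.05 falls further with any loss

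*Protocol*

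**What the plan says.** All references are to the protocol.

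- **Error rates and effects.** The Power Analysis sets beta and the sidedness of alpha ("0.20, and two-tailed", at 0.05). It works with two differences, "using a high projected mean difference of 10 points, and a low projected mean difference of 5 points".
- **Table and conclusion.** The sensitivity table has a row of 50 per arm, 5 points, SD 10, power .80. The text says that "the total sample size required would range from 26 to 138 patients" and concludes: "Therefore, a sample size of about 100 patients should be optimal for this study".
- **Enrolment.** Number of Subjects states: "We plan on enrolling 100 subjects overall, 25 subjects at the Tufts Medical Center site". Study Design fixes 1:1 allocation, so 50 per arm are randomized.
- **Losses.** Study Discontinuation/Termination begins "Patients will be discontinued from the study for the following reasons" and lists six, among them MADRS worsening, noncompliance and patient preference. Blinding and Controls offers open-label ziprasidone to those who do not finish the six weeks.
- **Analysis.** The primary comparison is by unpaired t-test and by mixed effects regression. The primary population is intent-to-treat, "including those who discontinue drug due to lack of efficacy or due to side effects"; the completer analysis is secondary.
- **Not stated.** There is no dropout rate, no inflation of the sample size and no expected number with an outcome.

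**The concern.** A two-sample power calculation counts patients who supply an outcome. Here that count equals the number enrolled, so the calculation holds only if every randomized patient supplies a full acute-phase change score. The protocol's own rules make that unlikely: it removes patients from the study, not just from drug, and a separate completer analysis has a purpose only if some do not complete.

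What is at stake is the meaning of the .80. It is the only figure in the protocol that ties 100 patients to a power. If the trial ends without a significant difference, readers will judge the result against it. If the real power for 5 points is 60% to 70%, a null result says much less than the protocol suggests.

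**Working it through.** **Inputs.** From the Power Analysis: two-tailed 0.05, difference δ = 5, SD σ = 10, n = 50 per arm, printed power .80. From Study Design: 1:1 allocation. Dropout rates of 10%, 20% and 30% are assumed, because the protocol gives none.

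**Formula.** For a two-sample t-test with n per arm, the noncentrality is λ = (δ/σ)·√(n/2) on 2n − 2 degrees of freedom. The normal approximation to the two-sided power is Φ(λ − 1.96), and to the one-sided power Φ(λ − 1.645).

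**Step 1: reproduce the printed row.** λ = 0.5 × √25 = 2.5.
- Two-sided: Φ(0.54) = 70.5%; exact t-test 69.7%.
- One-sided: Φ(0.855) = 80.4%; exact t-test 79.9%.

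The printed .80 is therefore a one-sided 0.05 figure. At the stated two-tailed level, 80% power needs 64 per arm by t-test (63 by the normal formula). About 10 points of power are missing before anyone leaves.

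**Step 2: observed values only, n = 50 × (1 − d).**

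| Assumed loss | n per arm | λ | Two-sided power | One-sided power (table's scale) |
| --- | --- | --- | --- | --- |
| 0% | 50 | 2.500 | 69.7% | 79.9% |
| 10% | 45 | 2.372 | 65.0% | 76.1% |
| 20% | 40 | 2.236 | 59.8% | 71.6% |
| 30% | 35 | 2.092 | 54.1% | 66.5% |

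On the two-sided scale the further loss is about 5, 10 and 16 points.

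**Step 3: mixed model on the weekly scores.** This takes the generalised least-squares information for the last-visit contrast, with monotone dropout spread evenly over the six post-baseline visits. Correlation and timing are assumed. The effective n is 50 times the fraction of information kept.
- AR(1) correlation 0.7: fraction 0.83 to 0.84 at 20% loss, power 61% to 62%; fraction 0.74 to 0.75 at 30% loss, power about 57%.
- Exchangeable correlation 0.85: fraction 0.89 to 0.92 at 30% loss, power 64% to 66%, a loss of 4 to 5 points from 69.7%.

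The ranges depend on whether some patients leave before any post-baseline rating. The model recovers part of the loss: little under AR(1) 0.7, most of it under high exchangeable correlation.

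**Step 4: all 100 kept in the intent-to-treat t-test.** n stays at 50 per arm, but patients who leave may contribute less effect. If 20% contribute none, δ = 5 × 0.8 = 4, λ = 0.4 × 5 = 2.0, and two-sided power is about 51%.

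**Step 5: the other scenarios in the table, two-sided t-test.**

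| δ | σ | 50 per arm | 40 per arm (20% loss) |
| --- | --- | --- | --- |
| 5 | 5 | over 99% | 99% |
| 5 | 10 | 70% | 60% |
| 5 | 15 | 38% | 31% |
| 10 | 10 | over 99% | 99% |
| 10 | 15 | 91% | 84% |

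The shortfall lies in the 5-point scenarios with SD 10 or more.

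**The case against.** **Sidedness is the prior error.** A reader might infer that the missing dropout allowance is why 80% is not reached. The arithmetic does not support that. With nobody lost, the row already has about 70% at the stated level. Dividing 50 by (1 − d) would not repair it: at 20% loss, 63 enrolled per arm leaves 50 with data and still 70%. This objection stands, and dropout has to be presented as an addition to it.

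**Leaving the study is not leaving the analysis.** The primary population is intent-to-treat, MADRS is rated weekly, and three of the discontinuation criteria need two successive visits, so many leavers will have post-baseline scores. The outcome is change in the acute phase, and Week 6 is not named as the time point. How leavers enter the t-test can properly be left to a statistical analysis plan. This also stands: the figures in Step 2 are the pessimistic case for the mixed model, and it would be wrong to read them as the power of the planned analysis. But the intent-to-treat label does not create later scores for patients no longer in the study, and keeping everyone can cost more through dilution (Step 4).

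**The row is inferred.** The text does not name the 50-per-arm row as its basis; it picks about 100 from a wide range and claims only reasonable prospects of detecting an effect. That is fair. Still, no other row gives 100, and 5 points is the low difference the protocol chose to plan for.

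**The visit grid shows no rating after early exit.** One might infer that none is made. The grid lists only planned weeks, and a termination visit is mentioned elsewhere, so this cannot be claimed either way.

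**Conclusion.** The point holds in a limited form. The protocol enrols exactly the number in its 5-point, SD 10 row and allows nothing for dropout, although it provides for patients leaving. At two-tailed 0.05 that row has about 70% power with complete data. Loss of outcomes takes it to about 65%, 60% and 54% at 10%, 20% and 30% for a t-test on observed values. The mixed model does somewhat better, and a t-test keeping all 100 with a diluted effect could do worse.

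The dropout rates, their timing, the visit correlations and the degree of dilution are all assumptions. What does not depend on them is that the printed .80 is too high for the stated test and that any loss of outcomes or dilution of the effect lowers it further.

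It does not follow that 100 patients is too few for every effect considered, or that the trial cannot run. A 10-point difference with SD 15 keeps about 84% at 20% loss. The defect is in a stated figure and is cheap to correct.

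**What to change.** Keep 100 patients and restate what they deliver:

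1. Recompute the sensitivity table at two-tailed 0.05.
2. State an assumed dropout rate, with its reason, and the resulting expected number per arm with an end-of-acute-phase MADRS (for example 40 of 50 if 20% is assumed).
3. Print the power at that number for differences of 5 and 10 points over the SD range, as in Step 5. If credit is claimed for the mixed model, give the correlation and dropout pattern assumed.
4. Remove the unqualified .80 for 50 per arm as support for the sample size.

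The cost is a few lines and one revised table, with no extra patients or visits. The downside is a less favourable stated power: about 60% instead of 80% for 5 points and SD 10 on the 20% example.
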